### Safety assessment

Data on all adverse events will be collected and included in medical reports, which will be forwarded to the health authorities. To ensure patient safety, if any adverse events occur at any time during the study, participants will be monitored for up to 4 weeks after study exit.

### Statistical analysis

Data will be expressed as means and standard deviations or medians and interquartile ranges for nonparametric variables. Two-way analysis of variance (ANOVA) for repeated measures will be used to evaluate averages before and after acute inspiratory muscle exercise, comparing the placebo (2 % of PImax) and intervention (60 % of PImax) loads. Pearson correlation coefficients will be used to evaluate the association between components of cardiovascular autonomic control and glucose levels. For nonparametric variables, Spearman correlation will be used. The statistical power will be 80 % and differences will be considered significant for *P* < 0.05. All analyses will be performed using SPSS Statistics for Windows, version 20.0 (IBM Corp., Armonk, NY, USA).

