## Methods/design

### Study design

This study is a randomized clinical trial with a crossover design.

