### Outcome measures

The difference in glucose levels before and after exercise (evaluated by continuous glucose monitoring systems; glucose level after exercise minus glucose level before exercise) is the primary outcome measure. The secondary outcome measures are: (1) changes in glucose variability, which will also be evaluated by continuous glucose monitoring systems through conventional (mean amplitude of glucose excursion, variation of glucose, coefficient of variation of glucose, and standard deviation of glucose) and non-conventional indices (spectral analysis and symbolic patterns: no variation); (2) changes in cardiovascular autonomic control, which will be evaluated by blood pressure variability and heart rate variability (measures of power spectral density of low frequency, high frequency and very low frequency bands). Table 1 shows the measures that will be evaluated to achieve the desired results.

**Table 1 Tab1:** Evaluated measures

Time point	Data collection	Measure	Outcomes
Pre-evaluation	Blood and urine analysis	Glycemia, HbA1c, microalbuminuria and creatinine	Metabolic responses
	Cardiovascular autonomic assessment	Ewing tests	Diagnosis of cardiovascular autonomic neuropathy
	International Physical Activity Questionnaire	Survey	Physical activity estimates
	Inspiratory muscle test	maximal inspiratory mouth pressure (PImax)	Inspiratory muscle strength
	Pulmonary function test	maximum voluntary ventilation, forced vital capacity, vital capacity, forced expiratory volume (1 s), forced expiratory volume (1 s)/vital capacity and forced expiratory volume (1 s)/forced vital capacity	Pulmonary flow and volume
	Rest electrocardiogram	12-lead electrocardiogram	Electrical activity of the heart
	Cardiopulmonary exercise testing	VO_2peak_, VCO_2peak_, R_peak_, VE_peak_, VE⁄VO_2peak_, VE⁄VCO_2peak_	Ventilatory and metabolic variables
At rest	Continuous glucose monitoring system	Glucose concentration	Glucose levels and variability
	Biopac system	Continuous recording of blood pressure	Blood pressure and heart rate variability in time and frequency domains
Controlled ventilation	Continuous glucose monitoring system	Glucose concentration	Glucose concentration and variability
	Biopac system	Continuous recording of blood pressure	Blood pressure and heart rate variability in time and frequency domains

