### Randomization

The randomization sequence will be generated by computer. Randomization to the low-resistance inspiratory muscle exercise group (2 % of maximal inspiratory pressure (PImax), placebo load) or the high-resistance inspiratory muscle exercise group (60 % of PImax, experimental load) will be performed by an investigator assigned exclusively to this task, who will not participate in the recruitment, assessment, or intervention phases of the study.

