### Study intervention

After baseline evaluations, all patients will be instructed to present to the laboratory, three times per week for 2 weeks, for completion of the intervention stage of the study protocol, as follows:Day 1: Placement of the continuous glucose monitoring system. Patients should arrive at 8:00 a.m. for device placement. Patients using beta blockers will be advised to discontinue their medication 24 hours before the next study visit.Day 2: Acute inspiratory muscle exercise protocol (2 % or 60 % of PImax). Patients should arrive at 10:00 a.m. and will be instructed to rest in the supine position for 10 min for collection of baseline glucose, continuous blood pressure, and heart rate measurements. Participants will then start controlled ventilation for 10 min. A 40-minute interval will be allowed to elapse before the start of acute inspiratory muscle loading. Pursuant to random group allocation, participants will receive loading to 2 % of PImax (low resistance, placebo load) for 10 min or to 60 % of PImax (high resistance, experimental load) until task failure. At the end of the exercise protocol, a 10-min recovery record will be obtained. Glucose levels will also be measured by capillary sample before and after the protocol reported above. Arterial oxygen saturation (SpO_2_) mean arterial pressure, end-tidal carbon dioxide, calf blood flow, and calf vascular conductance will be measured during all protocols.Day 3: Continuous glucose monitoring system removal. Patients will be instructed to return to the laboratory at noon for removal of the device.

One week following these interventions, all subjects will return to the study facility to repeat these procedures, but using another randomized load for inspiratory muscle exercises.

The experimental sessions will take place at the Hospital de Clínicas de Porto Alegre Exercise Pathophysiology Research Laboratory. All experiments will be performed in a temperature-controlled room and all subjects will be instructed to refrain from consuming caffeinated beverages and alcohol for at least 12 hours and from exercise for at least 24 hours prior to the evaluation. Continuous assessment of blood-glucose levels and blood pressure will be performed before, during, and after all protocols. Patients will be asked to follow their habitual diet and keep a detailed food intake record across the 3 days of continuous glucose monitoring system use.

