### Acute inspiratory muscle exercise

This protocol was developed by Dempsey *et al.* [44] to reduce diaphragm blood flow and cause fatigue. During the protocol, individuals will breathe continuously through a two-way valve (Hans Rudolph, 2600 series, Shawnee, KS, USA) with low resistance (2 % of PImax) connected to an inspiratory resistance obtained by a threshold inspiratory muscle trainer (DHDInspiratory Muscle Trainer, Chicago, IL) or, for higher inspiratory pressures (60 % of PImax), to a POWERbreathe® inspiratory muscle trainer (Southam, UK). Inspiratory pressure will be continuously recorded and displayed on a computer screen shared through a television, providing visual feedback; the 10-point Borg scale [45] will be used to access inspiratory effort at task failure. Inability to maintain breathing will be defined as a reduction of PImax to less than 80 % of the prescribed value during three consecutive breaths [38]. For the placebo experiments conducted at 2 % of PImax, measurements will cease at 10 min. The sequence of experiments, induction of the inspiratory muscle metaboreflex (60 % of PImax), or allocation to the placebo experiment (2 % of PImax), will be randomized, and experiments will be conducted 1 week apart.

In both protocols, baseline data will be collected during 10 min of spontaneous breathing. After this period, a controlled ventilation protocol will be initiated, and individuals instructed to maintain a breathing frequency of 15 breaths per min and a duty cycle (*T*_I_/*T*_Tot_) of 0.7 by listening to an audio signal with distinct inspiratory and expiratory tones for 10 min. Calf blood flow will be measured by venous occlusion plethysmography (Hokanson, TL-400, Bellevue, WA, USA) every 10 s in the non-dominant lower limb. Calf vascular conductance will be calculated as calf blood flow divided by mean arterial pressure [46]. Blood pressure will be monitored once a minute using an automated monitor (Dinamap, USA), and heart rate will be monitored continuously throughout the protocol.

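### The planned two-way ANOVA (load by before/after) has no period term for a two-session crossover, so an order effect on the glucose change enters the error or the load contrast

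*Protocol article*

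**What the plan says.** - Design (Study design): "This study is a randomized clinical trial with a crossover design".
- Sessions (Study intervention): a week after the first session every patient comes back and goes through the same steps, "but using another randomized load for inspiratory muscle exercises".
- Order (Acute inspiratory muscle exercise): "The sequence of experiments, induction of the inspiratory muscle metaboreflex" at the high load or the placebo run at the low load, is randomised, and "experiments will be conducted 1 week apart".
- Primary outcome (Outcome measures): the within-session change, "glucose level after exercise minus glucose level before exercise".
- Model (Statistical analysis): "Two-way analysis of variance (ANOVA) for repeated measures will be used to evaluate averages before and after acute inspiratory muscle exercise", comparing the two loads. The two factors are therefore time (before, after) and load. Neither this section nor any other names period, session or sequence as a model term.

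**The concern.** In a two-period crossover each patient's load contrast contains the load effect plus or minus any difference between first and second session, with the sign set by the order received. A model with only load and time cannot separate the two. Here the first session may be the patient's first sustained bout of loaded breathing, at the high load taken to task failure, so a response that differs between sessions is conceivable. The article neither reports nor rules out such an effect.

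At stake are the precision of the primary comparison and, if the orders end up unequal, the estimate itself. With 14 patients there is little room for either loss.

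**Working it through.** **Inputs from the article (Sample size and power calculation).** 14 patients including 10 % dropout, target difference 34 mg/dl, SD 30 mg/dl, power 80 %, type I error 5 % (two-sided assumed). The article does not say whether 30 is the SD per load or of the within-patient difference.

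**Reproducing the 14.** n = 2 × 30² × (1.96 + 0.84)² / 34² = 12.2; 12.2 / 0.9 = 13.6, rounded up to 14. Read as a count of crossover patients, this corresponds to SD 30 per load with no within-patient correlation, so an SD of the difference of 30 × √2 = 42.4. If 30 is already the SD of the difference, the same formula gives 6.1, which does not lead to 14. Both readings are carried below.

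**Which order effects reach the primary contrast.** Let D be a patient's change at 60 % minus change at 2 %.
- A shift that raises glucose equally before and after exercise in one session drops out of that session's change, and so out of D.
- A difference P between sessions in the change itself stays: D = load effect + P in one order, load effect − P in the other, plus error.

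With two loads and two time points, the load-by-time F test is the square of the paired t test on D. Without a period term:
- bias = P × (n1 − n2) / (n1 + n2), where n1 and n2 are the patients in each order;
- at 7:7 the bias is 0, but the variance estimated for D rises by P² × 14/13. For P = 20 that is 400 × 14/13 = 431, so the estimated SD goes from 42.4 to √(1800 + 431) = 47.2, or from 30 to √(900 + 431) = 36.5.

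**Power at 7:7, effect 34 mg/dl (simulation; P is assumed).**

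| P (mg/dl) | SD of D | Power, period ignored | Power, period in model | Type I error, period ignored |
|---|---|---|---|---|
| 0 | 30 | 0.97 | 0.97 | 0.05 |
| 10 | 30 | 0.97 | 0.97 | 0.04 |
| 20 | 30 | 0.93 | 0.97 | 0.02 |
| 0 | 42.4 | 0.79 | 0.79 | 0.05 |
| 10 | 42.4 | 0.77 | 0.79 | 0.04 |
| 20 | 42.4 | 0.72 | 0.79 | 0.03 |

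With the period term, type I error stays at about 0.05 throughout.

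**Unequal orders, 9:5, P = 20.** Bias = 20 × 4/14 = 5.7 mg/dl, which is 17 % of 34. Its sign depends on which order is larger and on the direction of P. The standard error is 30/√14 = 8.0 or 42.4/√14 = 11.3, so the bias is 0.7 or 0.5 of a standard error. Type I error with period ignored is about 0.05, because the inflated error offsets the bias. If the bias works against the effect, power is 0.81 against 0.96 with the term (SD 30), or 0.56 against 0.75 (SD 42.4). If it works with the effect, power is 0.98 against 0.96, or 0.85 against 0.75; that gain comes from the bias.

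**The case against.** The strongest reply is that the order is randomised, so over repeated randomisations an order effect averages out. The primary outcome is a within-session change, so most of what one would call a first-session effect (a general shift in glucose level, for example) cancels. Nothing in the article points to an order effect on the change, and an assumed 20 mg/dl is 59 % of the target difference (20/34). A separate analysis plan may also include the term. Most of this stands and limits the size of the point. It does not remove it: the trial will have one realised split of 14 patients, and the article commits to a specific two-factor model rather than leaving the model open.

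Four stronger readings are tempting, and the document does not support them.

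- *Patients are allocated to a load group rather than to an order.* The Randomization section does speak of "Randomization to the low-resistance inspiratory muscle exercise group", but the section on acute inspiratory muscle exercise states that the sequence is randomised.
- *The two orders will probably be unbalanced.* Under simple randomisation 7:7 would occur 21 % of the time and 9:5 or worse 42 %. The article says only that the list is computer generated. Blocking is a detail that a condensed article commonly omits.
- *Ignoring period inflates false positives.* At 7:7 the test is conservative, and at 9:5 it is about nominal. Inflation appears only at a more extreme split such as 10:4 (0.058 to 0.098 for P of 10 to 20 mg/dl, across both SDs).
- *The load main effect is the primary test, so a 34 mg/dl effect would show as 17.* No section says so. The outcome definition and the before/after comparison between loads, read together, point to load by time.

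**Conclusion.** The point holds as a defect in the stated model and should be fixed. It is not grounds to call the primary comparison invalid. Its size rests on an assumed period effect in the change. For 10 to 20 mg/dl with balanced orders, the cost is about 1 to 7 points of power, the upper end applying under the SD reading that reproduces the planned 14. For 20 mg/dl at 9:5 it is a 5.7 mg/dl bias of unknown sign. If there is no order effect on the change, the planned analysis loses nothing.

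**What to change.** In Statistical analysis, replace the two-factor model for the primary outcome with an analysis of the per-session glucose change (after minus before, as in Outcome measures) that has load and period as fixed effects. Two equivalent routes for patients with both sessions are sequence as a between-patient factor in the repeated-measures ANOVA, or a mixed model with patient as random effect. State that the load effect on the change, which is the same as load by time, is the primary test.

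The cost is wording and one degree of freedom. With no period effect and 7:7, power goes from 0.792 to 0.786 (SD of the difference 42.4) or from 0.974 to 0.972 (SD 30). If the orders turn out unequal the price is higher: at 9:5 with no period effect it is 0.79 to 0.75, or 0.97 to 0.96. The article reports the trial as still recruiting, so the change can be made before results are known.

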## Abstract

**Background:**

Physical exercise reduces glucose levels and glucose variability in patients with type 2 diabetes. Acute inspiratory muscle exercise has been shown to reduce these parameters in a small group of patients with type 2 diabetes, but these results have yet to be confirmed in a well-designed study. The aim of this study is to investigate the effect of acute inspiratory muscle exercise on glucose levels, glucose variability, and cardiovascular autonomic function in patients with type 2 diabetes.

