### Sample size and power calculation

According to preliminary results obtained in our laboratory [31], the sample size was estimated in 14 individuals with type 2 diabetes, allowing for a dropout rate of 10 %. This sample size would detect a 34 mg/dl difference in glucose levels between the intervention inspiratory load of 60 % and the placebo inspiratory load of 2 %, taking into account a standard deviation of 30 mg/dl, a statistical power of 80 %, and a type I error rate of 5 %. WinPepi software was used to calculate the sample size.

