## Discussion

Exercise programs have traditionally emphasized aerobic exercise, because of its well-known cardiovascular [47], metabolic [48], and autonomic benefits in type 2 diabetes [24, 49]. Resistance training also has favorable effects on muscle strength, abdominal fat, insulin sensitivity [22], and blood pressure [21]. Furthermore, combined exercise is also beneficial for metabolic parameters [19, 20] and glucose variability in subjects with type 2 diabetes [18]. However, as not all patients tolerate conventional exercise and some find it difficult to adhere to fitness programs, alternatives must be developed to enable these patients to obtain the benefits of physical exercise. Inspiratory muscle training is a novel exercise modality that has demonstrated impressive beneficial effects on inspiratory muscle strength and resistance [29, 50] and in reduction of glucose variability [30]. However, given the relatively small sample size of our preliminary study [30], we planned to examine this question in greater depth through a new study with a larger sample of patients with type 2 diabetes, seeking to confirm that a single bout of inspiratory muscle exercise may provide a benefit similar to that achieved with aerobic exercise on glucose levels and glucose variability. In brief, this study will be conducted to evaluate glucose levels, glucose variability, and cardiovascular autonomic responses at rest, during, and after a session of acute inspiratory muscle exercise performed under two resistance loads (low, 2 % of PImax; high, 60 % of PImax).

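### The trial seeks to confirm a benefit on glucose variability, but no one of its six unranked variability indices, each judged at P < 0.05, is fixed as deciding that claim

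*Protocol article*

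**What the plan says.** Four places in the protocol article bear on this.

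- **Outcome measures** names one primary outcome, the change in glucose level across the exercise session. Glucose variability is secondary and has six measures. Four are conventional: "mean amplitude of glucose excursion, variation of glucose, coefficient of variation of glucose, and standard deviation of glucose". Two are non-conventional: spectral analysis and the symbolic no-variation pattern. They are not ranked. Autonomic control is a further secondary outcome, with three spectral bands for each of two signals (blood pressure and heart rate).
- **Statistical analysis** plans a two-way repeated-measures ANOVA comparing the two loads and sets a single threshold: "differences will be considered significant for" P < 0.05. It draws no line between primary and secondary outcomes.
- **Discussion** describes the trial as "seeking to confirm that a single bout of inspiratory muscle exercise may provide a benefit", and the sentence goes on to name both glucose levels and glucose variability as the target of that benefit.
- **Sample size and power calculation** sizes the trial on glucose level alone: "This sample size would detect a 34 mg/dl difference in glucose levels", "taking into account a standard deviation of 30 mg/dl", 80 % power and 5 % type I error.

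**The concern.** A confirmatory claim needs a rule, fixed in advance, for when it has been met. For glucose level there is one: a single primary measure tested at 5 %. For glucose variability the article states the ambition to confirm and a threshold for each comparison, but not which of six measures carries the claim, or whether one, most or all must be significant.

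This is more than a detail left to an unseen analysis plan. The article itself fixes a flat P < 0.05 rule and itself uses confirmatory language for a quantity measured six ways, and the two do not fit together. With 14 patients, one index could fall below 0.05 by chance while the others do not. The published plan would not stop that result from being presented as confirmation that inspiratory exercise lowers glucose variability, even if the primary comparison showed nothing.

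**Working it through.** **Inputs**

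- Threshold per comparison: 0.05 (Statistical analysis). Sidedness is not stated; two-sided is assumed.
- Number of variability indices: 4 conventional + 2 non-conventional = 6 (Outcome measures).
- Patients: 14 (Sample size and power calculation).
- Correlation between indices: not in the article. Values from 0 to 0.95 are assumed.
- One between-load contrast per index, and no true effect on any index.

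**Step 1. The plan's own figure.** The two-means formula with the stated inputs gives n = 2 × (1.960 + 0.842)² × 30² / 34² = 2 × 7.85 × 0.7785 = 12.2. Dividing by 0.9 for dropout gives 13.6, so 14, as stated. (Rounding up to 13 first gives 14.4, so 15.) Every input concerns glucose level. The 5 % in that calculation belongs to the primary comparison, and the number of secondary indices does not change it.

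**Step 2. Six independent indices.** The chance of at least one P < 0.05 in either direction is 1 − 0.95⁶ = 0.265. The chance of at least one significant *reduction*, nominally 2.5 % per index, is 1 − 0.975⁶ = 0.141.

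**Step 3. Correlated indices.** One-sample t tests on within-patient contrasts were simulated with 14 patients and 60,000 replicates, using a common correlation among the six:

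| Correlation | Any index P < 0.05 | Any significant reduction |
|---|---|---|
| 0 | 26.4 % | 13.8 % |
| 0.3 | 24.4 % | 12.2 % |
| 0.5 | 21.3 % | 10.9 % |
| 0.7 | 17.1 % | 8.6 % |
| 0.8 | 14.7 % | 7.2 % |
| 0.9 | 11.3 % | 5.7 % |
| 0.95 | 9.2 % | 4.5 % |

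**Step 4. A more realistic pattern.** The conventional indices come from the same glucose series and should be closely related; the spectral and symbolic measures may be less so. With the four conventional indices correlated at 0.8–0.95 and the other pairs at 0–0.5, the five settings run gave 16.5–19.7 % for any significant index and 8.5–9.7 % for any significant reduction.

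**Step 5. One named index.** With a single deciding index and a single contrast, the figures return to 5 % and 2.5 %.

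Six is the smallest reasonable count. Glucose variability evaluation describes several oscillatory components and several symbolic patterns, Table 1 lists variability at four stages of the session, and a two-way ANOVA tests more than one effect. Testing more of these would raise the figures.

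**The case against.** The strongest reply has four parts.

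*Multiplicity rules for secondary outcomes usually sit in an analysis plan, and this is a condensed article.* True, and their absence alone would be no finding. What remains is what the article does state: one flat threshold, alongside an intention to confirm a claim about variability.

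*There is a hierarchy.* One outcome is primary, the rest are labelled secondary, and the sample size rests on the primary. This stands in full. It protects the primary conclusion but does not say how the variability claim is to be judged.

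*The trial's stated aim is to investigate, not to confirm.* A reader might take the Abstract's remark that "these results have yet to be confirmed in a well-designed study" as a confirmatory aim. It is background on earlier results, and both the Abstract and the Background state the aim as investigating an effect. The confirmatory wording rests on one Discussion sentence, itself softened by a *may*. But that sentence describes what this trial sets out to do, and it names variability.

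*Nothing says that one significant index would be enough.* Correct. A reader might infer that the investigators mean to claim success on any single index; the article does not say so. It does not exclude it either, nor require all six. The error rates above are therefore conditional on that reading. Near-redundant indices would bring the inflation down to about twofold.

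**Conclusion.** The point holds for the variability claim only. The article announces an intention to confirm a benefit on glucose variability and leaves open which of six unranked indices decides it. If any one index at P < 0.05 were taken as confirmation, the two-sided chance of a false positive would be about 26 % under independence, about 21 % at correlation 0.5 and about 11 % at 0.9. For a false reduction it would be about 5–14 % against 2.5 %. These figures assume the correlations, one contrast per index and no true effect.

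Two stronger readings are not supported. A reader might add the six autonomic band powers and quote 1 − 0.95¹² = 46 % for twelve measures. But a chance finding in blood pressure or heart rate variability cannot confirm a fall in *glucose* variability, and the Discussion's confirmatory clause does not name autonomic control. The relevant family is six. A reader might also conclude that the trial's overall type I error is uncontrolled; the single primary test is untouched.

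This limits what can be concluded about variability and should be corrected. It does not put the primary result in doubt.

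**What to change.** Before results are known (Trial status reports that recruitment is under way):

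1. Name one variability index already listed as the key secondary outcome, and base any claim of reduced variability on its between-load contrast at two-sided 0.05. The coefficient of variation is one example; the choice belongs to the investigators.
2. Label the other five variability indices, the autonomic band powers and the correlations exploratory, and report them with 95 % CIs.
3. In the Discussion, limit the confirmatory wording to the primary outcome and that one index, or drop it for variability.

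Testing the key index only after a significant primary result would be stricter, but it is optional and the point does not depend on it.

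The cost is wording. Measurements, visits and sample size do not change, and every index is still reported. The downside is that fewer measures can support a formal claim.
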